### Sample Size

A formal sample size calculation is not essential for this exploratory trial, which primarily seeks to establish feasibility, effects on candidate mechanisms, and initial signals of efficacy. In planning, we aimed to determine the sample size in such a way as to establish the feasibility of the methodology for conducting an RCT and delivering the EMIcompass intervention to youth with early mental health problems and initial signals of the efficacy of EMIcompass in reducing psychological distress as a candidate primary outcome (see Statistical Analysis Plan [113] for further detail) as a basis for a future definitive trial. For the latter, previous studies of third-wave CBT [72,114], including compassion-focused interventions [68,77], suggest that these types of interventions may yield clinically meaningful reductions in psychological distress of moderate to large effect size. This is consistent with the initial findings from an uncontrolled phase I pilot study [53]. However, even if the effect size for the main effect of condition on psychological distress (primary outcome) in this exploratory RCT is small, a power simulation in the R environment indicated that a sample size of N=80 participants (40/40, 50% experimental, 40/40, 50% control condition) would be sufficient to detect a small effect size of 0.3 across the postintervention 4-week follow-up with a power of 81% when testing at α=.05 for the effect of condition (experimental vs control condition) on psychological distress using linear mixed modeling, which will be tested using a Wald-type test of no difference between the two conditions across both time points against the two-sided alternative hypothesis that the conditions are, on average, different across the two follow-up time points (given the exploratory nature of this trial), while controlling for baseline psychological distress and group status. At the 4-week follow-up, we expect an attrition rate of 15%, resulting in a loss to follow-up of approximately 6 individuals per condition on average (Figure 1). Therefore, we will randomize a total of 92 participants at baseline, leaving 80 participants at follow-up to detect a small effect size of 0.3 at this time point. This sample size is also sufficient to test the criteria for establishing feasibility. Simulation studies on power and accuracy for multilevel mediation models with continuous variables [115] and our recently completed multilevel moderated mediation analysis of EMA data [42] suggest very little bias in parameter estimates with samples of this size (and 40 repeated measures, on average, per participant).

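### Sample Size: 15% attrition from 92 leaves 78, not 80, and the simulated power is for the two-visit average, not for the 4-week visit to which the 0.3 effect is attached

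*Protocol article*

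**What the plan says.** All the figures are in the Sample Size section of the protocol article. It reports that "a power simulation in the R environment indicated that a sample size of N=80 participants" (40 per condition) is enough. The claim itself is worded as follows: "sufficient to detect a small effect size of 0.3 across the postintervention 4-week follow-up with a power of 81% when testing at α=.05". The planned test is of Wald type in a linear mixed model. Its alternative is described as the "two-sided alternative hypothesis that the conditions are, on average, different across the two follow-up time points". The model adjusts for two covariates, in the article's words "while controlling for baseline psychological distress and group status".

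On attrition at the 4-week follow-up, the section says: "we expect an attrition rate of 15%, resulting in a loss to follow-up of approximately 6 individuals per condition on average". The number randomised is set at 92. The section describes the result as "leaving 80 participants at follow-up to detect a small effect size of 0.3 at this time point".

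The Statistical Analysis section repeats the 1-df test of the average difference over the two follow-ups. It treats the contrasts at each visit as estimates with 95% confidence intervals, taken from a second model with a time by condition interaction.

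**The concern.** Two things in the attrition sentences do not follow from what comes before them.

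First, the attrition rate, the loss per arm, the number randomised and the number remaining cannot all be true together. The loss appears to have been taken as a percentage of the completers wanted, not of the participants randomised.

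Second, the detectable effect of 0.3 is carried from a contrast averaged over two visits to a single visit. An average of two imperfectly correlated measurements is less variable than either one, so a sample size that suffices for the average does not automatically suffice for one visit.

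The trial is meant to supply planning estimates for a definitive trial. A reader who takes the sentence at face value would expect the 4-week estimate to be more precise than the simulation supports.

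**Working it through.** **Attrition**

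Inputs from Sample Size: 92 randomised, 15% attrition, about 6 lost per condition, 80 remaining. Allocation is 1:1 (Randomization and Blinding), so 46 per arm.

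- The plan's 92 is reproduced by 80 × 1.15 = 92, and its 6 per arm by 0.15 × 40 = 6. Both apply 15% to the completers.
- Applied to those randomised: 0.15 × 46 = 6.9, about 7 per arm, and 92 × 0.85 = 78.2, so 78 remain (39 per arm).
- Losing 6 of 46 is 6/46 = 13.0%.
- Keeping 80 at 15% loss needs 80/0.85 = 94.1, rounded up to 95 (96 for equal arms).

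**What the 81% implies**

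The article gives neither the correlation between the two follow-ups (ρ) nor the correlation of baseline with each follow-up (r), so the 81% cannot be reproduced independently. Without adjustment, 40 per arm and an effect of 0.3 SD give only 26.8% power (two-sided α = 0.05). The 81% must therefore rest on a substantial gain from averaging and baseline adjustment.

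I read 0.3 as a fraction of the single-visit SD and assume equal variances and equal r at both visits. The variance factors after baseline adjustment are then:

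- average of two visits: v = (1 + ρ)/2 − r²
- one visit: v₁ = 1 − r² = v + (1 − ρ)/2

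The second exceeds the first unless ρ = 1.

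With the normal approximation, power = Φ(0.3/√(2v/n) − 1.96). Setting this to 81% with n = 40 per arm gives v = [0.3/(√0.05 × (1.960 + 0.878))]² = 0.2235.

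**Cost of 39 instead of 40 per arm, averaged test**

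√(2 × 0.2235/39) = 0.1071 and 0.3/0.1071 − 1.96 = 0.84, so power is 80.0%.

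**Power at the 4-week visit alone**

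The averaged test is held at 81% with 40 per arm. The detectable effect at 80% power is 2.80 × √(2v₁/40).

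| Assumed ρ | Implied r | v₁ | Power for 0.3, 40 per arm | Power for 0.3, 39 per arm | Detectable effect (SD), 40 per arm |
|---|---|---|---|---|---|
| 0.50 | 0.73 | 0.474 | 50% | 49% | 0.43 |
| 0.70 | 0.79 | 0.374 | 59% | 58% | 0.38 |
| 0.83 | 0.83 | 0.307 | 68% | 67% | 0.35 |
| 0.90 | 0.85 | 0.274 | 73% | 72% | 0.33 |
| 0.95 | 0.87 | 0.249 | 77% | 76% | 0.31 |
| 1.00 | 0.88 | 0.224 | 81% | 80% | 0.30 |

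A noncentral t calculation gives about one point less at ρ = 0.5 and 0.83 (49% and 67% with 40 per arm).

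**The case against.** The best defence is that little depends on these sentences. The article says a formal calculation is not essential for an exploratory trial and refers to the statistical analysis plan for detail. The loss per arm is hedged as approximate. The tested hypothesis is the averaged one, and the visit-specific contrasts are only estimated. A participant seen only at postintervention still contributes to the mixed model, so 78 is not necessarily the effective number for the averaged test. The Results section reports that all 92 have been randomised, so the design can no longer change.

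Most of this stands, and it limits the weight of the point. It does not remove the point: 6.9 does not round to 6, the 80 is stated without a hedge, and a separate analysis plan cannot change what the article says was simulated.

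Three stronger readings are tempting and not supported:

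- A reader might infer that the article claims 81% power at 4 weeks. It does not. It attaches 81% to the effect across both follow-ups and states no power for the 4-week contrast.
- A reader might infer that 4-week power is at most 68%. That value holds only if ρ = r = 0.83. It lies within the range and is not a ceiling.
- A reader might put 4-week power far lower by assuming ρ = r = 0.7 (47%) or 0.5 (34%). Under those correlations the averaged test itself would have about 61% or 48% power, which contradicts the plan's 81%. They do not show what follows from the plan.

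**Conclusion.** The point holds as a minor correction in two parts.

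1. The attrition figures are inconsistent as written. The consequence is about one power point on the averaged test (81% to about 80%), and that only if 4-week completers alone are counted.
2. The statement that 80 participants suffice for 0.3 at the 4-week visit has no calculation behind it. With equal visit variances and equal baseline correlations, single-visit power is below that of the average unless the two follow-ups correlate perfectly. Taking the 81% as given, it is about 50% to 77% for ρ from 0.5 to 0.95, with a detectable effect of about 0.43 down to 0.31 SD at 80% power.

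The direction follows from the variance formula. The size depends on correlations and on a scale for 0.3 that the article does not state. None of this shows that the averaged test is underpowered or that the planned analysis is wrong.

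**What to change.** In Sample Size:

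- Reconcile the four attrition figures. State either 13% attrition (6 per arm) leaving 80, or 15% attrition (about 7 per arm) leaving 78 with about 80% power for the averaged test.
- Delete the last four words of the sentence on the number remaining, so that the 0.3 and the 81% apply only to the contrast averaged over both follow-ups. Alternatively, keep a 4-week statement and report the power for that contrast from the trial's own simulation, with the correlations it used.

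The cost is a few words and one or two figures, or one further output from the existing simulation. No participants are added and the analysis does not change.

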
### Randomization and Blinding

Participants will be randomized at a 50:50 ratio to the experimental or control condition at the level of the individual participant after completion of the baseline assessment. Block randomization in blocks of four will be performed by an independent research assistant through a computer-generated sequence, with stratification for the three stages (ie, stages 1a, 1b, and 2). The assessors will be blind to the allocation of participants when assessing outcomes at postintervention and follow-up. Any data specific to the intervention group (eg, clinical feasibility) will be stored in a separate database. Breaks in masking will be documented, and another (blinded) researcher will repeat the assessment to maintain masking.

### Assessment of Safety

Serious adverse events (SAEs) will be monitored throughout the entire study period and reported to the accredited Medical Ethics Review Committee, the Data Monitoring and Ethics Committee (DMEC), and, where required, the Trial Steering Committee (TSC). SAEs are any serious incidents that result in death, persistent or significant disability or incapacity that require hospitalization, or life-threatening situations. SAEs are not expected to occur as a result of the intervention. If there are doubts about safety or ethical concerns, the TSC will terminate the trial. The DMEC will advise on safety and ethical concerns, monitor evidence for harm by the intervention (eg, SAEs) in the experimental condition, and review whether these events are in line with expectations. If deemed necessary, the DMEC can recommend to the principal investigator (PI) and TSC for interim analyses to be conducted and the trial to be terminated prematurely.

### Statistical Analysis

The primary objective of this exploratory RCT is to establish the feasibility of the trial methodology and intervention delivery and initial signals of efficacy on the candidate primary outcome (ie, psychological distress) as a basis for a future definitive trial. In addition, this trial seeks to obtain parameter estimates (95% CI) for the effects on primary and secondary candidate mechanisms and candidate secondary outcomes. A detailed Statistical Analysis Plan [113] has been agreed with the DMEC and the TSC and has been preregistered and published on the Open Science Framework. It was registered while collecting the data before study completion and accessing the locked database. Descriptive statistics will be used, and CIs will be constructed as appropriate to compute basic sample characteristics and address the primary aim of establishing the feasibility of the trial methodology and intervention delivery based on the criteria described above and in further detail in the Statistical Analysis Plan using three categories (in line with a traffic light system): (1) feasibility fully established (green), (2) feasibility established, but study procedures need to be modified (yellow), and (3) feasibility not established (red) [113]. The analysis of candidate mechanisms and initial signals of efficacy has been described in detail in the Statistical Analysis Plan [113] and will be an intention-to-treat analysis or an available case analysis following intention-to-treat principles, with data from all participants entered into the analysis, including those who have low adherence to or who will drop out from the intervention. We will make every effort to assess all participants at postintervention and 4-week follow-up. Linear mixed modeling in Stata 16 will be used to compare candidate mechanisms and outcomes between experimental and control conditions at postintervention and 4-week follow-up. The primary candidate outcome of psychological distress measured at postintervention and 4-week follow-up will be entered as the dependent variable and psychological distress measured at baseline, group status (3-level factor), time (2-level factor), and condition (2-level factor) as independent variables. The main effect of condition on psychological distress will be parameterized so that it reflects the difference between the two conditions at the two follow-up time points (ie, postintervention and 4-week follow-up), which will be tested (at α=.05) by a Wald-type test with df=1, which tests the joint null hypothesis of no difference at both follow-up time points against the alternative hypothesis that there is, on average, a difference across the two follow-up time points. In addition, given the exploratory nature of this trial, with the main goal of establishing feasibility and obtaining parameter estimates for a future definitive RCT, 95% CI for the two time-specific contrasts of a time×condition interaction term will be inspected to obtain estimates for the differences across conditions at each of the two time points, with a time × condition interaction and a baseline psychological distress×time interaction added as independent variables to the previous model. Within-subject clustering of repeated measures (postintervention and 4-week follow-up) will be taken into account by including a level-2 random intercept and allowing the models’ level-1 residuals to be correlated with a completely unstructured error variance-covariance matrix. The model will be fitted using restricted maximum likelihood estimation. The analysis of secondary candidate outcomes and primary and secondary candidate mechanisms will, in principle, follow the same steps, focusing on 95% CIs (rather than P values at α<.05). Multilevel moderated mediation analysis of EMA data will be used to explore whether the effects of condition on primary (ie, psychotic, manic, anxiety, or depressive) symptoms are mediated via stress reactivity, threat anticipation, negative affective appraisals, and interpersonal sensitivity [42]. As participants will be randomly assigned to experimental and control conditions, no differences across conditions are expected in other study parameters (sociodemographic characteristics, alcohol or substance use, and childhood trauma). No statistical tests will be performed on these study parameters at baseline.

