#### Experimental Condition: EMIcompass Intervention Plus TAU

The EMIcompass intervention will be delivered by trained psychologists within a 6-week period in addition to TAU to individuals allocated to the experimental condition. TAU consists of all the treatment individuals received before inclusion in the study, including their general practitioner, psychiatrist, and clinical psychologist, except for treatment using elements of third-wave CBT. The manualized EMIcompass intervention consists of four biweekly sessions (three training sessions and one review session) with a duration of 45-60 minutes administered face-to-face or using a certified and encrypted video conferencing system and a 6-week compassion-focused EMI. An optional on-demand session will be offered if participants are unable to complete tasks between sessions or report acute psychological distress so that a scheduled session cannot be followed as per the manual. The EMI, which translates the training from the intervention sessions into individuals’ daily lives, will be administered through a smartphone-based app (movisensXS, movisens GmbH) running on dedicated study smartphones. The first three sessions are based on elements of compassion-focused therapy [68]. In line with our pilot study [53], compassion-focused therapy principles and techniques are introduced in these guided sessions. The first session aims to familiarize the participants with the app offering EMI. Further, practical tasks to activate the soothing system, as a key emotion regulation system in compassion-focused therapy, are presented and trained together with the psychologist, as described elsewhere [88]. Face-to-face sessions also offer the opportunity to reflect on the progress and problems participants face with EMI. In the last session, progress with all tasks will be reviewed and subjective improvement in, compliance and satisfaction, and acceptance of the EMIcompass intervention will be assessed.

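### The stated K10 model and power description make no allowance for clustering by psychologist, although only the experimental arm has psychologist-delivered sessions; if outcomes vary by psychologist, the condition effect's precision is overstated

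*Protocol article*

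**What the plan says.** All of this is in the protocol article.

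- **Allocation.** Under Randomization and Blinding, the unit is the individual participant, 1:1, stratified by clinical stage.
- **Delivery.** Under Experimental Condition: "The EMIcompass intervention will be delivered by trained psychologists within a 6-week period in addition to TAU to individuals allocated to the experimental condition". There are four manualised sessions of 45-60 minutes plus a six-week app component. Under Control Condition, the other arm continues its existing care and has no trial psychologist.
- **Model.** Statistical Analysis sets follow-up K10 as the outcome, with baseline K10, stage, time and condition as fixed effects, a 1-df Wald test of condition at α=.05, and restricted maximum likelihood. On clustering it says: "Within-subject clustering of repeated measures (postintervention and 4-week follow-up) will be taken into account by including a level-2 random intercept". Level-1 residuals are unstructured. No psychologist level appears.
- **Power.** Sample Size reports an R simulation for "a sample size of N=80 participants (40/40, 50% experimental, 40/40, 50% control condition"), described as "sufficient to detect a small effect size of 0.3 across the postintervention 4-week follow-up" and "with a power of 81% when testing at α=.05", adjusting for baseline distress and stage. It mentions no psychologist variance, number of psychologists or design effect.

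Both sections refer to a separate statistical analysis plan, which is not shown.

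**The concern.** This is a partially nested design. Participants treated by the same psychologist may have correlated outcomes, while controls share no trial psychologist. A model whose only cluster is the participant treats experimental-arm participants as independent of one another. If they are not, the standard error of the condition effect is too small for inference to psychologists in general, the Wald test rejects too often, and the confidence intervals are too narrow.

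The trial is exploratory, but this still matters. The K10 comparison is tested at α=.05 and read as an efficacy signal. The analyses of secondary outcomes and mechanisms follow the same steps and report 95% intervals. The estimates are intended to inform a definitive trial, and overstated precision would carry into its planning.

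**Working it through.** **Inputs from the protocol article (Sample Size):** two-sided α = 0.05; effect size 0.3; 40 analysed per arm; power 81%.

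**Inputs assumed, because the article does not give them:** k = 2 to 8 psychologists; ICC = 0.01 to 0.10 on the baseline-adjusted outcome; equal caseloads m = 40/k; one psychologist per participant.

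**Step 1. The stated 81%.** An unadjusted two-sample comparison with d = 0.3 gives z = 0.3/√(2/40) = 1.342 and power Φ(1.342 − 1.960) = 26.8%. For the mean of two follow-ups adjusted for baseline, SE² = (2/40) × [(1+ρ)/2 − r₀²], where r₀ is the baseline to follow-up correlation and ρ the correlation between follow-ups. Power of 81% needs the bracket to be about 0.22, for example r₀ = ρ = 0.83. With r₀ = ρ = 0.5 to 0.7, power is about 47% to 61%. The article defines neither the metric of 0.3 nor the correlations, so 81% can be neither confirmed nor refuted. I therefore take it as the starting point: noncentrality 1.960 + 0.878 = 2.838.

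**Step 2. Partial nesting.**
- Experimental-arm design effect: DE = 1 + (m − 1) × ICC
- Variance ratio for the arm difference: VR = (1 + DE)/2
- Factor by which the SE is understated: √VR
- Real two-sided alpha of the stated test: 2 × [1 − Φ(1.960/√VR)]
- Power with the correct SE: Φ(2.838/√VR − 1.960)

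Example, k = 4 and ICC = 0.05: m = 10; DE = 1 + 9 × 0.05 = 1.45; VR = 1.225; √VR = 1.107. Alpha = 2 × [1 − Φ(1.771)] = 7.7%. Power = Φ(2.564 − 1.960) = 72.7%.

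| k | ICC | DE | VR | SE factor | Real alpha | Power |
|---|---|---|---|---|---|---|
| any | 0 | 1.00 | 1.000 | 1.00 | 5.0% | 81.0% |
| 8 | 0.01 | 1.04 | 1.020 | 1.01 | 5.2% | 80.2% |
| 4 | 0.01 | 1.09 | 1.045 | 1.02 | 5.5% | 79.3% |
| 8 | 0.05 | 1.20 | 1.100 | 1.05 | 6.2% | 77.2% |
| 4 | 0.05 | 1.45 | 1.225 | 1.11 | 7.7% | 72.7% |
| 2 | 0.05 | 1.95 | 1.475 | 1.21 | 10.7% | 64.7% |
| 4 | 0.10 | 1.90 | 1.450 | 1.20 | 10.4% | 65.4% |
| 2 | 0.10 | 2.90 | 1.950 | 1.40 | 16% | 52.9% |

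**Step 3. Simulation check** (20,000 runs per setting, independent-errors test, no true effect). Rejection rates were 5.1% (k = 4, ICC 0), 7.2% (k = 4, ICC 0.05), 10.1% (k = 4, ICC 0.10) and 16.0% (k = 2, ICC 0.10), in line with the formulas.

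**Step 4. Sensitivity to the ICC scale.** If the ICC is placed on the unadjusted outcome and the Step 1 bracket is 0.2235, the extra variance at k = 4, ICC 0.05 is 0.05/4 − 0.05/40 = 0.01125, against 0.05 × 0.2235 = 0.01118. Then VR is about 2.01, alpha about 17% and power about 52%. On that basis the table is the milder case.

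The alpha column does not depend on whether 81% is right. The power column does.

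**The case against.** **The analysis plan is not shown.** It may already contain a psychologist analysis, and an article need not repeat it. That stands as a caution: if it does, the sponsor need only say so. It does not remove the point, because the article states the primary model down to its random effect, residual structure and estimator. A psychologist level would make it a different model.

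**The estimand is a choice.** If inference is conditional on the psychologists who delivered this trial, their average effect is part of the treatment effect and the stated standard error is not understated on this account. For a first look at efficacy that is defensible. This stands, which is why the main model need not change.

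**The premises are thin.** The article does not say how many psychologists there were, how participants were assigned, or whether one psychologist delivered all four sessions. Manualised sessions and the app component may keep psychologist variance small. This stands.

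**Stronger readings a reader might infer, and why they fail:**
- That the standard error is too small as a matter of fact. This needs an ICC above zero, which the article does not show.
- That the R simulation assumed independence. This is inferred from a short description; the code is not shown.
- That the protocol itself treats psychologists as a source of K10 variation, because it rates therapist competence and measures working alliance. The ratings are feasibility and fidelity measures, and the alliance scale is listed among other measures; neither is linked to the K10 analysis.

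**Conclusion.** The point holds in conditional form. As stated, the K10 model and the power description make no allowance for psychologist clustering, and the design has it in one arm only. If the psychologist ICC exceeds zero and the result is meant to generalise beyond the trial's own psychologists, the standard error is understated and power is below 81%.

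The size cannot be fixed from the article. Within the assumed range it runs from trivial to a threefold false-positive rate, with 4 psychologists and ICC 0.05 as an illustrative middle case. The power figures use a normal approximation; a small-sample correction would lower them further. Because the trial is exploratory and declares a formal sample size calculation unnecessary, this is a recommended improvement and does not invalidate the main analysis.

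**What to change.** Keep the main K10 model. Before the database is locked (planned by September 2021 under Results, Overview):

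1. Prespecify a sensitivity analysis with the same fixed effects plus a psychologist random effect in the experimental arm only, each control being a singleton, and a small-sample degrees-of-freedom correction. Report it beside the main result.
2. If there are too few psychologists to estimate the variance, or cases were shared, report the condition confidence interval recomputed over a fixed ICC range such as 0 to 0.10.
3. Report the number of psychologists and their caseloads.
4. If the R simulation included no therapist variance, say in Sample Size that the 81% assumes a therapist ICC of zero.

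Do not make the ICC range a rule for declaring a signal. Its upper bound would be arbitrary, and with 2 psychologists at ICC 0.10 power would be about 53%.

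**Cost.** An amendment to an analysis plan that has been preregistered and agreed with the oversight committees, and one more model fit. Expect a somewhat wider sensitivity interval, an imprecise ICC and a less favourable power statement. No participants or study procedures are added.
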